## Abstract

**Background:**

Over 10 million operations are carried out every year in the UK, improving millions of lives. While most operations are low-risk, some result in patients having poor outcomes. Preoperative assessment evaluates a patient’s health prior to surgery to identify risks and where possible minimise them through optimisation. However, this preoperative assessment often takes place close to the planned date of surgery, meaning there is little time to optimise patients’ health. Early preoperative screening is the process of evaluating a patient’s health earlier in the surgical pathway. In 2023, NHS England introduced a new programme where all hospitals were to implement early screening, triaging, risk assessment and health optimisation with the aim of increasing safety through reduced perioperative complications, increased efficiency (e.g., through reductions in last-minute cancellations), reductions in length of hospital stay, and identifying people who can undergo surgery without requiring an overnight stay. Here we describe the protocol to examine the implementation and impact of this new programme.

**Methods:**

A mixed methods research design will be used to evaluate this new programme. We will conduct a formative implementation evaluation using rapid qualitative methods consisting of interviews with staff members and patients across three broadly representative specialities (colorectal cancer surgery, repair of abdominal aorta and knee replacement) and observations of key meetings held regarding implementation activities. An interrupted time series analysis will address patient centered outcomes (days alive and out of hospital at 30, 180 and 365 days after surgery; postoperative hospital length of stay; emergency re-admission within 30 days) using routinely collected electronic health records.

**Discussion:**

This study will provide lessons on the barriers and facilitators to implementation and will highlight staff and patient experiences of the new programme. It will also assess impact on patient centred outcomes using routinely collected hospital data and quasi-experimental research methods.

## Introduction

Over 10 million operations are carried out every year in the UK, improving millions of lives [1]. While most operations are low risk, some result in patients having poor outcomes. Several challenges can lead to poor outcomes after surgery, many of which can be modified if detected early enough, and appropriately managed: examples include poor physical fitness (“deconditioning”), behavioural factors such as tobacco and alcohol dependence, and poorly managed individual comorbidities (e.g., diabetes, hypertension) [2]. These challenges can be compounded in patients with ‘multimorbidity’ – that is, where a patient has more than one long term condition. In the UK, half of all 65-year-olds have multimorbidity, and this gets more common amongst older patients and people living in deprived areas [3]. Patients with multimorbidity are less likely to be in the best condition to undergo an operation: they are therefore more likely to have their operation cancelled at short notice (because it might not be safe for them to have surgery), or have complications or poorer outcomes if they do have their operation [4,5]. This means that, at present, surgery provided by the NHS in England may not be as safe or as efficient as it could be.

Patient safety is a priority for healthcare systems. In safe systems, patients would be less likely to experience avoidable harm, both from their own conditions, and from the care and treatments provided to them. International estimates suggest that of 421 million hospitalisations annually, there are 42.7 million adverse events or unsafe experiences, making avoidable harm the 14th worldwide leading cause of death and serious illness [6]. Amongst the highest risk clinical settings are Surgical, Perioperative, Acute and Critical carE (SPACE) services. In the UK, SPACE services treat >25 million NHS patients annually [7,8], SPACE services are therefore, being rapidly redesigned to expand capacity and increase productivity, using largely untested pathways of care, some of which include the complex transition between primary and secondary care.

Surgery causes physiological stress [9]. For patients who are deconditioned, have poorly managed long-term conditions or multimorbidity, there is a higher risk of complications during and after surgery, which can impact patient outcomes for years after surgery [2,10]. Preoperative assessment evaluates a patient’s health prior to surgery. The aim of this assessment is to identify risks and where possible minimise them through optimisation - “the process of supporting and working with a patient to get their health in as good a state as possible before surgery” [11]. of any co-existing medical conditions. However, preoperative assessment often takes place close to the planned date of surgery, meaning there is little time to optimise the patients’ health. This can leave a difficult decision between a late notice cancellation of the operation or, in other cases, because the surgery is urgent proceeding with surgery that carries a greater risk of post-operative complications than if long-term health conditions had been optimised. Early preoperative screening is the process of evaluating a patient’s health earlier in the surgical pathway [11,12]. This process identifies health risks that may be modifiable through prehabilitation and optimisation and aims to improve the patient’s physical and or psychological condition in advance of surgery [11,12]. This may include the process of risk scoring and shared decision making. Early preoperative screening aims to lead to an optimisation plan that both the patient and surgical team agree with [12]. Potential benefits include better patient health outcomes and fewer short notice cancellations [3,5,13].

In 2023, all NHS hospitals in England were asked to implement a programme of early screening, triaging, risk assessment and health optimisation [11]. This included pre-assessment questionnaires and establishing an expanded perioperative care workforce. The directive was published in the 2023/24 NHS Standard Contract [14] followed by guidance published in May 2023 [11].These teams could consist of, for example, care co-ordinators, nurses and perioperative physicians who carry out assessments of health needs to identify surgical risk factors and inform pre- and post-operative care. The team would identify low-risk patients who do not need to attend face-to-face preoperative assessment and patients who could be treated in elective hubs focused on providing High Volume Low Complexity (HVLC) surgery. These services are intended to facilitate early shared decision making and optimisation of patient health, increasing patients’ suitability and readiness for surgery. A key anticipated benefit of these changes is increased safety through reduced perioperative complications (both in terms of complications from surgery, and the psychological harms associated with last-minute cancellations) [11]. The programme may also increase efficiency, e.g., through reductions in last-minute cancellations, reductions in length of hospital stay, and identifying people who can undergo surgery without requiring an overnight hospital stay [11].

The requirement for an early screening, triaging, risk assessment and health optimisation programme (hereinafter referred to as “the programme”) to be implemented was included in the NHS 2023/24 contract with the stipulation that the programme was to be implemented “no later than 31 March 2024”. This is a national programme, with implementation taking place across multiple NHS hospital organisations, in diverse geographic and socioeconomic contexts and within a variety of surgical pathways. It is likely that implementation progressed variably across different clinical and organisational settings. In addition, some settings or specialties (e.g., bariatric surgery) [15] have more well-established multidisciplinary preoperative pathways which aim to optimise comorbidities and reduce the risk of patients undergoing surgery without critical modifiable health issues having been addressed. In this manuscript we describe the mixed methods approach we will adopt to examine the implementation and impact of the new screening programme.

## Study aims and research questions

### Study aims

To evaluate staff, patient and carer experiences of the programme across NHS Trusts and factors influencing this, to generate lessons learnt from this programme and for future programmes of this kind.i) Explore patient experiences of the programme and their involvement in decision-making throughout the early screening and optimisation process.ii) Examine the perceptions of healthcare providers on the feasibility, benefits, and challenges of the programme.Evaluate the effectiveness of early preoperative screening and optimisationi) Assess how early preoperative screening impacts patient outcomes, surgical complications, cancellation rates, and cost implications.ii) Determine the extent to which early screening influences patient readiness, overall health, and recovery outcomes.

### Research questions

Implementation evaluation

Programme design and implementationi) How was the programme designed, and what factors influenced this?ii) How are different NHS settings implementing the programme and to what extent have the activities been implemented?iii) What are the experiences of those implementing and delivering the programme?iv) What are the barriers and facilitators for different NHS sites in implementing the programme?Patient experiencei) What are patient perceptions and experiences of the preoperative optimisation process?ii) To what extent do patients feel informed and supported in shared decision-making regarding their surgical care?iii) Has the implementation of this programme resulted in changes to patient care as anticipated?

### Effectiveness evaluation

Patient Outcomes and Health Impacti) How does early preoperative screening impact rates of postoperative complications and patient recovery times?ii) What effect does early screening and optimisation have on rates of short-notice surgical cancellations?iii) To what extent does early identification and optimisation of health risks influence long-term health outcomes for patients?Cost implications and Resource Allocationi) What are the cost implications of early preoperative screening and optimisation on healthcare resources and system efficiency?

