### Quantitative methodology: Secondary outcomes

The secondary outcomes of this study are postoperative length of stay in hospitals and emergency re-admission within 30 days, as these are related to patient safety in peri-operative setting [29]. Both variables will be constructed using extracted data fields in HES data. In addition, we will examine days spent in critical care [30]. Finally, we will consider related costs using Healthcare Resource Groups (HRG) codes in HES datasets and linking them to the National Tariff.

In addition, we plan to assess the impact of early preoperative screening on the incidence of short-term cancellations by linking data from the Theatre Productivity Dataset with Perioperative Care Census conducted by NHS England [31]. These datasets collect information at the hospital site level, and are currently in their infancy. Data quality and completion will be assessed prior to any analyses to ensure findings are reliable and robust.

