$\beta_{\text{5}}$ represents the change in the slope of the trend post the intervention

Details of this methodology are available elsewhere [37].

In our analysis, by stratification, we will examine variations in time trend patterns in geographic location and patients characteristics including age groups, gender, ethnicity and deprivation measured using Index of Multiple Deprivation quantiles. We will use region of residence and local integrated care board in HES data to indicate geographical locations. Age will be grouped as 18–44, 45–65, 66–79, and 80 plus [38]. Ethnicity will be grouped based on ONS 2021 census ethnic categories, including White, Asian and Asian British, Black and Black British, Mixed or multiple ethnic groups, and Other ethnic group. In addition, we will explore variations in NHS hospital sites.

We will also check for seasonality impacts through sensitivity analyses such as using time stratified model, periodic functions or flexible spline functions that are detailed elsewhere [39]. The timing of rollout of the intervention was likely to be different across hospitals, therefore, we will conduct a sensitivity analysis with different definitions of the intervention period (i.e., early implementation period- 1^st^ March to 31^st^ Aug 2023 vs late implementation period – 1^st^ Sep 2023–31^st^ March 2024). Given the dramatic impact of Covid on health services, we will also assess the impact of a shorter baseline period of between Jan 2018 to Feb 2020. In addition, concurrent national programmes that target similar outcomes, such as Getting it Right First Time (GIRFT) [40], could confound our results. We will conduct sensitivity analyses that will stratify by different time periods to adjust for relevant national programmes if there are well-documented dates of implementation and can be distinctly modelled within our time series. We will conduct complete case analyses. Stata 17 (StataCorp) and R 4.2.2 (R Core Team, 2022) will be used to conduct the analysis.

Finally, to examine short-term cancellation, we will conduct descriptive data analysis and describe short-term cancellation data across different time periods and geographical regions.

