The quantitative effectiveness evaluation has several important limitations. First, the study lacks a randomised control group because the early screening programme was implemented nationally across England in all specialties and we only have data for hospitals in England. Without a control group, this makes a single interrupted time series analysis the most suitable approach. Second, the analysis cannot definitively link the intervention to individual patients, relying instead on the timing of the programme’s implementation. This is due to the level of uncertainties around exact timing of the programme’s rollout and differences in pre-existing established early screening and optimisation services across different hospitals in the country. To deal with this, we will conduct several sensitivity analyses using different start dates for the intervention period to account for both early and late implementation and also stratify our analyses by regions or hospitals using results from our short-term cancellation data and qualitative study. Third, this design is susceptible to confounding from co-occurring events and policy changes in the same period. To address confounding events such as in the case of COVID, we will be conducting a sensitivity analysis using a shorter pre-COVID baseline period and by using our qualitative findings to provide context for any observed changes. Fourth, unmeasured confounding may also bias our results. Fifth, the analysis relies on routinely collected hospital data, which may have data quality concerns [43]. To address this, we will conduct thorough data cleaning and preparation to ensure our findings are robust.

We acknowledge that programme success is more complex than simple statistical improvements. It is possible that the programme’s success is demonstrated by widening access to surgery for higher-risk patients who would have been previously excluded, which might result in static or even worsened postoperative complication rates and lengths of stay. To account for this, we will also monitor changes in underlying patient characteristics, such as the percentage of patients in the most deprived quintile of the Index of Multiple Deprivation, which is strongly correlated with multimorbidity rates [44].

Table 4 provides a summary outlining the key components of the study.

**Table 4 pone.0335129.t004:** Summary Table outlining key components of the study.

	Qualitative	Quantitative

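### Complications are asked about but have no outcome, cancellations are asked about as an effect but only described, and cancellation results may also be used to form hospital or regional strata

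*Protocol article*

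**What the plan says.** Under Study aims, the effectiveness aim is to "Assess how early preoperative screening impacts patient outcomes, surgical complications, cancellation rates, and cost implications". The Effectiveness evaluation list under Research questions, repeated in Table 4, turns this into four questions. The first covers complications and recovery together: "How does early preoperative screening impact rates of postoperative complications and patient recovery times". The second concerns cancellations and is worded causally: "What effect does early screening and optimisation have on rates of short-notice surgical cancellations". The third is about health in the longer term, and the fourth about costs and efficiency.

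The primary outcome is DAOH at 30 days, with DAOH at 180 and 365 days also assessed. The secondary outcomes section states: "The secondary outcomes of this study are postoperative length of stay in hospitals and emergency re-admission within 30 days". It adds critical care days, costs from HRG codes and the National Tariff, and the incidence of short-term cancellations. The cancellation data are to come from linking the Theatre Productivity Dataset with the Perioperative Care Census. That section says the aim is to assess impact on cancellations, but warns that these sources are site-level and immature.

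The statistical analysis section applies segmented regression to DAOH, length of stay, emergency re-admission, critical care days and costs. For cancellations it says: "to examine short-term cancellation, we will conduct descriptive data analysis". Finally, to deal with uncertain rollout timing and services that already existed, the Discussion plans to "stratify our analyses by regions or hospitals using results from our short-term cancellation data and qualitative study".

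**The concern.** There are three separate mismatches.

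- **Complications.** They are in the aim, the first question and Table 4, and the Introduction presents fewer of them as a main expected benefit. The Discussion even considers that complication rates might stay level or worsen. No listed outcome would show this.
- **Cancellations.** The question asks for an effect and the outcome section speaks of impact, but the analysis is descriptive. Tabulating cancellations by period invites a causal reading that it cannot support.
- **Stratification.** The programme is meant to reduce cancellations. If strata are defined by cancellation results, hospitals are grouped partly by what happened after the programme started. The strata may then be read as degrees of implementation when they also reflect other things.

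At stake are one stated aim that can be approached only through proxies, one causal question answered with description, and a subgroup comparison that could be misread.

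**Working it through.** No sample size, error rate or event count bears on this point, and the plan gives no figure to reproduce. The check sets each question beside the outcomes and the analyses.

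| Question | Outcome named | Analysis named |
|---|---|---|
| 1a Complications | None; DAOH, re-admission and critical care days are proxies | None for a complication rate |
| 1b Recovery times | Length of stay, DAOH | Segmented regression |
| 2 Cancellations | Incidence of short-term cancellations, two linked sources | Descriptive only |
| 3 Long-term outcomes | DAOH at 180 and 365 days | Segmented regression |
| 4 Costs | HRG and National Tariff costs | Segmented regression |

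Splitting the first question gives 4 + 1 = 5 items. One has neither outcome nor model (1a) and one has an outcome but no effect model (2), so 5 − 1 − 1 = 3 are fully served. The two gaps differ in kind: a missing outcome in half of question 1, and a missing effect analysis in question 2.

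**Is DAOH a complication outcome?** The Primary outcome section says DAOH is related to in-hospital complications. That supports DAOH as a measure but does not yield a complication rate. DAOH also moves with discharge practice, re-admission and death, so a change in DAOH cannot be attributed to complications.

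**What could stratifying on cancellations do?** The model in the statistical analysis section has a baseline level (β0), a pre-intervention trend (β1), and level and slope changes for the intervention period (β2, β3) and the post-intervention period (β4, β5).

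1. Fitted within a stratum, β0 and β1 belong to that stratum. Stable differences between hospitals in capacity or case mix go into these terms and not into β2 to β5.
2. A problem arises if strata depend on cancellation results from after March 2023, or on change in them. A hospital whose case mix became lighter for unrelated reasons could show both fewer cancellations and better DAOH. The Introduction supplies the link: patients with multimorbidity are more likely both to be cancelled at short notice and to have poorer outcomes. Such a hospital would enter the favourable stratum without having implemented anything.
3. The reverse is also possible. The Discussion says a successful programme may widen access to higher-risk patients and leave outcomes static or worse.
4. The article does not say how cancellation results would define strata, or from which period. Neither the size nor the direction of bias can therefore be derived.

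**The case against.** The strongest reply has four parts.

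- **Proxies.** The first question is compound. Its recovery half is covered, and DAOH, re-admission and critical care days all bear on complications. This stands, and it limits the gap to half of one question.
- **Cancellations.** Describing immature, site-level data is a reasoned restriction, and an effect model would be harder to defend. This also stands. What remains is that the question and the reference to impact promise more than the analysis gives.
- **Stratification.** The sentence refers to regions or hospitals and draws on the qualitative study too; it does not say that strata are cut on cancellation rates. The Integrated approach section separately plans an implementation typology for the five study sites. This stands, so the risk is conditional on how the sentence is carried out.
- **Condensation.** An article may leave detail to the full analysis plan. That would excuse a missing code list. It does not remove the mismatch, because the article itself states the questions, the outcomes and the modelled outcomes, and they do not agree.

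A reader might infer more: that cancellations have no outcome at all, that stratification replaces their analysis, or that the strata will produce a spurious dose-response in favour of the programme. The documents do not support these readings. Cancellations have a named outcome and sources, stratification is additional to their description, and each stratum's own level and pre-trend absorb stable differences, while the Discussion allows a case-mix shift in the unfavourable direction.

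**Conclusion.** The point holds in three limited parts. The complications half of the first effectiveness question has no complication outcome and none in the segmented regression. The cancellation question asks for an effect but receives description only. Using cancellation results to form strata could condition on a post-intervention outcome, with bias of undetermined size and direction.

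The extent is two of five question components not fully served, plus one underspecified stratification. DAOH at 30 days and its national analysis are untouched. The third part assumes that strata would use cancellation results from the implementation or post-intervention periods, which the article neither states nor excludes. The mismatches should be resolved before the analysis plan is finalised, because a stated aim otherwise rests on proxies and a secondary comparison could mislead.

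**What to change.** **Complications.** Add one secondary outcome, postoperative complications coded from HES diagnoses and procedures, with the code list and time window fixed in advance, and analyse it with the same segmented regression. The Data sources section says HES holds these fields; that the bespoke extract includes them is an assumption, since the field list (S4 File) is not shown. The cost is a code list and one more model. The downside is that complication coding is imperfect and may change over time, which an interrupted time series can mistake for an effect. The alternative is to remove complications from the aim, the question and Table 4, and state that DAOH is only a proxy.

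**Cancellations.** Reword the question, and the reference to impact under Secondary outcomes, as descriptive. The cost is wording, and giving up a causal claim that the data are not ready to support.

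**Strata.** Define them from implementation information fixed before outcomes are seen, and not from cancellation results. Candidates are the NHS England indication of degree of implementation described under Sampling, where available, and the typology for the five sites. State that this will not cover all hospitals: the NHS England list covers sites that agreed to be contacted, and the typology covers five. The documents do not show whether the Perioperative Care Census holds implementation data, so that needs checking before it is relied on.

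The quantitative timeline provides for revising the analysis plan during months 0–9, while data access is awaited, so these changes can be made then at little cost.
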